## **Abstract:**

**Purpose:** Telemedicine-based structured exercise programs have the potential to benefit patients with chronic low back pain (CLBP). However, evidence-practice gaps persist, including low exercise adherence and insufficient focus on mental health. Consequently, further research is warranted to clarify the impact of telemedicine-supported structured exercise programs on patients with CLBP.

**Patients and methods:** This randomized controlled trial will include patients with CLBP who have not received exercise therapy in the past three months. Participants in the trial group will receive patient education, health coaching, and home-based exercise therapy via mobile health (mHealth) applications loaded with wearable device integration. Those in the control group will receive conventional treatment, comprising patient education and written instructions for home exercises. Disability including pain intensity will be assessed as primary outcomes using the Roland-Morris Disability Questionnaire (RMDQ) and the Numerical Rating Scale (NRS) at baseline, 4 weeks, and 8 weeks. Statistical analyses will depend on assumptions such as homogeneity of variance and sphericity: if met, a two-factor, three-level repeated measures analysis of variance will be used; otherwise, a linear mixed-effects model will be employed.

**Keywords:** low back pain; telemedicine; exercise; study protocol; randomized controlled trial.

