## **Material and methods**

### ***Aims of the study***

#### **Primary objective**

The primary objective of this study is to assess the effect of a telemedicine-supported structured exercise program on physical function including pain in adult CLBP patients in

Chengdu, Sichuan Province, China, compared with traditional therapy (paper-based exercise therapy).

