## Primary outcomes

CLBP severity will be measured using the Numerical Rating Scale (NRS), which ranges from 0 (no pain) to 10 (severe pain). Patients select a single number (0–10) that best represents their current level of pain. The NRS is widely used due to its simplicity, ease of administration, and reliable detection of pain severity.

The Roland Morris Disability Questionnaire (RMDQ) evaluates functional status in patients with low back pain. It consists of 24 items specifically related to limitations caused by low back pain. Each item is scored as 1 (yes) or 0 (no), yielding a total score between 0 and 24, where higher scores indicate greater functional impairment.

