## ***Statistical analysis***

All analyses will follow the Consolidated Standards of Reporting Trials (CONSORT) guidelines. Baseline measurements, group comparability, and descriptive characteristics will be assessed. Because patient dropout can occur for various reasons, data analyses will include both intention-to-treat (ITT) and per-protocol (PP) approaches. PP analysis considers only participants who complete the entire trial post-randomization, whereas ITT analysis includes follow-up data from all randomized participants. While PP analysis can exaggerate between-group differences, ITT analysis minimizes bias and loss to follow-up, generally producing more conservative estimates. Therefore, ITT analysis will be used as the primary method to prevent overstating effectiveness. The primary endpoint of interest is assessed after eight weeks of treatment.

All statistical analyses will be performed using IBM SPSS, version 26.0.1, with two-tailed tests ( $\alpha=0.05$ ) determining statistical significance. At baseline, categorical variables (e.g., sex, occupation, education level) will be compared between trial and control groups using chi-square tests. Continuous variables (e.g., age, BMI, pain intensity, duration of low back pain) will undergo a normality test. If the data follow a normal distribution, results will be expressed as mean  $\pm$  standard deviation (SD) and analyzed using independent-samples T-tests or Mann-Whitney U tests. Otherwise, the median (interquartile range) will be reported, and nonparametric tests will be applied. If the data meet the assumptions of homogeneity of variance and sphericity, a two-factor, three-level repeated-measures analysis of variance (group $\times$ time) will be conducted; otherwise, a mixed-effects model will be used.

According to the International Spine Conference, a two-point change in pain intensity (NRS scale: 0–10) signifies a minimum clinically important difference (MCID). Chi-square tests will compare the proportion of patients in each group who achieve MCID. Cohen's criteria will be used to evaluate the effect size across all outcome measures. No interim or subgroup analyses

are planned. An ITT approach will be used to address missing data for the primary outcome, and multiple imputation will minimize missing values.

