## Discussion

The primary objective of this study is to compare the efficacy of a telemedicine-supported structured exercise program with a paper-based exercise therapy program in improving pain among patients with CLBP in Chengdu, Sichuan Province, China. Current international guidelines strongly recommend exercise and behavioral therapy as first-line treatments for persistent chronic pain, emphasizing the importance of patient self-management. In line with these recommendations, the telemedicine-supported TG focuses on establishing a home-based self-management model.

Telemedicine replaces face-to-face physical therapist guidance with app-based monitoring, wearable devices, and the WeChat platform, thereby reducing time and geographic constraints while allowing patients to perform sustainable home-based exercises. This approach is reinforced by the pioneering use of wearable devices, which objectively document exercise duration (reflecting adherence) and capture patients' behavioral patterns. By drawing on diagnostic opinions from multiple pain experts, the wearable system can recommend personalized exercise regimens for CLBP patients. Changes in behavioral patterns before and after treatment serve as an objective indicator of therapeutic efficacy. The deep learning system can also track shifts in pain perception and fear of movement by monitoring protective behaviors, while weekly WeChat conferences bolster patients' trust in therapists and encourage adherence through group interactions. Patient education aims to alter pain-related beliefs, highlight the importance of healthy habits for pain relief, and promote an active lifestyle to manage ongoing CLBP progression. Beyond pain and physical function, this study also assesses pain cognition to capture a comprehensive view of outcomes.

In conclusion, this trial will investigate the impact of a telemedicine-supported structured exercise program on patients with CLBP in Chengdu, Sichuan Province, China. The results may offer a more effective home-based self-management model, ease the medical burden of CLBP, and inform public health and preventative strategies worldwide. The long-term sustainability and cost-effectiveness of telemedicine supported interventions will be the focus of future research.

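### Two primary outcomes, an unadjusted 0.05 and no statement of whether one or both must succeed: the error rate and power of the primary claim are left undetermined

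*Protocol*

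**What the plan says.** The Abstract names two instruments as primary: "Disability including pain intensity will be assessed as primary outcomes using the Roland-Morris Disability Questionnaire (RMDQ) and the Numerical Rating Scale (NRS". The Primary outcomes section lists the same two, each in its own paragraph and without ranking them: "CLBP severity will be measured using the Numerical Rating Scale (NRS), which ranges from 0 (no pain) to 10 (severe pain" and "The Roland Morris Disability Questionnaire (RMDQ) evaluates functional status in patients with low back pain".

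The Statistical analysis section sets one significance level for everything: "All statistical analyses will be performed using IBM SPSS, version 26.0.1, with two-tailed tests", that is, "two-tailed tests ( $\alpha=0.05$ ) determining statistical significance". It gives no split, order or adjustment. It then writes in the singular, "The primary endpoint of interest is assessed after eight weeks of treatment", without saying which of the two outcomes is meant.

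The Sample size section describes one repeated-measures analysis of variance at alpha 0.05 with power 0.8. It gives 58 patients, or 78 after 25% dropout, and does not say whether the effect size of 0.3 refers to NRS or RMDQ.

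The primary objective appears in two versions. Under Primary objective it is the effect "on physical function including pain in adult CLBP patients". The Discussion opens by giving it as a comparison "with a paper-based exercise therapy program in improving pain among patients with CLBP", with function left out.

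**The concern.** With two primary outcomes, the success rule decides what the stated 5% and 80% mean. If a significant result on either outcome makes the trial positive, two tests at 0.05 give more than a 5% chance of a false primary claim. If both must be significant, the 5% is safe, but 80% power for one test is not 80% power for the pair. The protocol takes neither position, and its singular endpoint and pain-only objective point to yet another reading with one decisive outcome.

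Advance commitment matters more than usual here. Under Randomization and blinding the trial is open to participants and assessors, and both primary outcomes are self-reported.

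**Working it through.** **Inputs from the protocol.** Effect size 0.3, alpha 0.05 two-tailed, power 0.8, correlation among repeated measures 0.5, 2 groups, 3 time points, 58 evaluable, 25% dropout, 78 in total (Sample size); 1:1 allocation (Study design).

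**Input not in the protocol.** The correlation r between the NRS and RMDQ test statistics. The stated 0.5 is a correlation between time points and cannot stand in for it, so a range is shown.

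**Step 1: reproduce the stated sample size.** Take the group-by-time test with f = 0.3 and the G*Power effect-size option labelled as in SPSS:

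- noncentrality = f² × (N − 2) × (3 − 1) = 0.09 × 56 × 2 = 10.08
- degrees of freedom = 2 and (58 − 2) × 2 = 112
- power at N = 58: 80.8%; at N = 56: 79.2%

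So 58 is the smallest even total reaching 80%. Dropout: 58 / 0.75 = 77.3, rounded up to 78. Both figures match. The protocol does not name the option. Under it the 0.5 correlation does not enter. Other G*Power variants match less well: the between-group test gives 78.5% at N = 58, and the default interaction option needs only 20 patients. The sample size is therefore reproducible, for one test of one outcome.

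**Step 2: error rate if either outcome suffices.** For independent tests, 1 − 0.95² = 0.0975. For correlated tests, 1 − P(|Z1| < 1.96 and |Z2| < 1.96) with (Z1, Z2) bivariate normal:

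| r (assumed) | At least one false positive, either direction | At least one false claim of benefit (nominal 2.5%) |
|---|---|---|
| 0 | 9.75% | 4.9% |
| 0.3 | 9.5% | 4.8% |
| 0.5 | 9.1% | 4.5% |
| 0.7 | 8.3% | 4.2% |
| 0.9 | 7.0% | 3.5% |

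**Step 3: error rate and power if both are required.** A false claim then needs a false positive on at least one outcome that has no effect, alongside significance on the other, so its probability is at most 5%. Joint power at N = 58, with the planned effect on both outcomes:

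- independent outcomes: 0.808² = 0.65
- fully correlated outcomes: 0.81

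The stated 80% is met only near the upper end.

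**Step 4: cost of testing one outcome at 0.025**, as in the first step of Holm. Using the same calculation as Step 1, power at N = 58 falls from 80.8% to 72.0%. Restoring 80% at 0.025 would take 68 evaluable patients (80.2%), and 68 / 0.75 = 90.7, so 91 randomised.

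**The case against.** The strongest objection is that a multiplicity procedure often sits in the statistical analysis plan. That plan is not at hand, although the Acknowledgments mention help in developing one. Silence on a procedure would therefore be no finding. This stands, and the point does not rest on silence. The protocol itself fixes a flat 0.05, moves from two primary outcomes to one unnamed endpoint, and gives two primary objectives. A later plan would have to override or reconcile that text.

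A reader might infer that the trial has a 9% false-positive rate. The documents do not support that as a fact. It requires that a win on either outcome counts, which the protocol never says, and a moderate correlation, which it does not give.

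A reader might also infer that the decisive outcome is free to be chosen once results are known. That goes too far. Both instruments are fixed in the Abstract, the Primary outcomes section and Table 3, and week 8 is fixed as the main time point. The Introduction names pain and activity limitation together, and the Discussion later mentions physical function. Its pain-only sentence is an inconsistency to align and does not replace the outcomes section.

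Finally, each outcome's own test remains valid at 5%, and a reader of the results would see both. That is correct and limits the severity, but it does not say what a positive trial is.

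**Conclusion.** The point holds in this form: the protocol leaves the success rule for its two primary outcomes open, and its own statements about the primary endpoint and objective do not agree. The consequence depends on the rule:

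- **Either outcome suffices:** 7.0% to 9.75% chance of at least one false positive for r from 0.9 to 0. For benefit alone it is 3.5% to 4.9%, against 2.5%.
- **Both required:** error at most 5%, but joint power between about 65% and 81% at 58 evaluable patients, so the stated 80% is not assured.

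The first range rests on an assumed NRS-RMDQ correlation. The second rests on the planned effect applying equally to both outcomes and on the group-by-time calculation that reproduces 58. The sample size itself is not wrong on this point. This should be fixed before results are seen. It does not invalidate the design.

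**What to change.** Before results are seen, state one order for the week-8 comparison: test the first primary outcome at 0.05, and test the second at 0.05 only if the first is significant. This holds the error for the pair at 5%, costs the first outcome no power, and leaves 58 evaluable and 78 randomised unchanged. The price is that no confirmatory claim can be made for the second outcome if the first fails.

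If the sponsor cannot rank the outcomes, use Holm across the two. Power for an outcome tested at 0.025 is then 72.0% instead of 80.8% on the protocol's own calculation. That is a lower bound, because the outcome is tested at 0.05 once the other has passed.

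In either case, name the outcome to which the sample size refers. Use the same primary-outcome wording in the Abstract, Primary objective, Primary outcomes, Statistical analysis and Discussion. With a fixed order the change is to wording only, in the protocol and the trial registration, with no effect on data collection.

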## **Introduction**

Globally, low back pain (LBP) is the leading cause of disability, defined as pain located between the lower costal margin and the upper gluteal fold, with or without leg pain. Chronic low back pain (CLBP) refers to LBP lasting more than three months. Approximately 80% of individuals experience at least one episode of LBP in their lifetime, with about half recovering within 2–3 weeks and the remainder gradually developing CLBP. CLBP is a major contributor to disability in both developed and developing countries, ranking sixth in overall disease burden. In China, the annual prevalence of adult LBP ranges from 20.88% to 29.88%, underscoring its

significance as a public health issue. As a global public health concern, CLBP significantly disrupts daily life and work, causing pain, limited function, anxiety, depression, and reduced working hours.

Growing evidence indicates that baseline anxiety, depression, and low levels of physical activity correlate with increased pain, greater disability, and reduced quality of life in CLBP. Exercise therapy can alleviate pain through both central and peripheral mechanisms, including promoting cortical reorganization and modulating pro- and anti-inflammatory cytokines. By enhancing muscle strength, endurance, and electrical activity, exercise also improves spinal stability and relieves pain. Several meta-analyses have shown core stability and motor control training to be more effective than other therapies in reducing pain and disability among CLBP patients. However, exercise therapy alone is often insufficient because CLBP patients tend to engage in sedentary behaviors and may lack motivation, leading to fear avoidance and suboptimal adherence. Poor adherence in CLBP patients may make exercise therapy less effective, leading to concealment of the true efficacy. Unsupervised exercise further raises risks of injury, and although it can mitigate pain and disability, it often suffers from poor compliance. Semi-structured interviews reveal that younger patients favor visual or dynamic support, while older patients prefer coaching and supervision. Health coaching, grounded in behavioral change theory, promotes healthier lifestyles and can improve self-management and adherence. Nevertheless, in-person supervision or coaching is time-intensive and costly, and long-term efficacy may be jeopardized by recurrent symptoms when patients must continue exercising at home.

To optimize home exercise for CLBP, telemedicine—which harnesses the Internet, mobile devices, and other digital platforms—has shown strong potential for prevention, treatment, and health promotion. Research indicates that telemedicine enhances treatment adherence and lowers healthcare costs for various conditions. When structured exercise programs are delivered via telemedicine, patients can conveniently access personalized information and real-time guidance, improving pain, physical function, and overall quality of life compared with usual care. Although a systematic review of 12 clinical trials suggests low to moderate evidence for

telemedicine's effectiveness in alleviating pain intensity and improving function in CLBP, challenges persist in achieving high exercise adherence, adequately addressing mental health factors, and incorporating objective outcome metrics.

In response to these gaps, we will conduct a randomized controlled trial using a wearable-device–integrated app to remotely monitor home exercises for patients with CLBP. The wearable device and a deep learning system will capture and analyze movement characteristics to identify completed exercises and protective behaviors, offering an objective measure of adherence while highlighting psychological factors such as fear and catastrophic thinking. By detecting whether they complete the movement and whether there is a problem movement, the patient can be fed back to improve their exercise compliance. To support ease of use, the app has been streamlined, and dedicated training and phone support will be provided for older adults. Nicholl et al. developed a related mobile app for LBP self-management as part of the self-BACK project, offering algorithm-based digital interventions. Our study, however, includes weekly video supervision and health coaching, and employs a wearable device capable of detecting specific movements and protective behaviors rather than only step counts, potentially offering more precise assessments of adherence and psychological shifts. Ultimately, this trial will compare a telemedicine-supported structured exercise program (TG, trial group) to traditional therapy (CG, control group) in reducing pain and activity limitation among patients with CLBP following conservative treatment discharge.

## **Material and methods**

### ***Aims of the study***

#### **Primary objective**

The primary objective of this study is to assess the effect of a telemedicine-supported structured exercise program on physical function including pain in adult CLBP patients in

Chengdu, Sichuan Province, China, compared with traditional therapy (paper-based exercise therapy).

## **Secondary objective**

1.To assess the impact of a telemedicine-supported structured exercise program on quality of life, and psychopathological symptoms in adult CLBP patients in Chengdu, Sichuan Province, China, compared with traditional therapy (paper-based exercise therapy).

2.To assess the impact of a telemedicine-supported structured exercise program on exercise compliance and pain fear or pain catastrophic imagery in adult CLBP patients in Chengdu, Sichuan Province, China, compared with traditional therapy (paper-based exercise therapy).

## **Study design**

This is a randomized controlled trial with two parallel arms, conducted in an open-label, difference-test manner, following a 1:1 allocation ratio, within a single-center over a span of 8 weeks. The trial follows the recommendations of the Standard Protocol Items: Recommendations for Interventional Trials (SPIRIT) statement. A completed SPIRIT checklist can be found in online supplemental material I. This study has received approval from the Ethics Committee of West China Hospital, Sichuan University. Any significant protocol modifications will be submitted to the Biomedical Ethics Committee of West China Hospital, Sichuan University for review. The study protocol has been registered at the Chinese Clinical Trial Registry (ChiCTR2300071560). The current study protocol is the sixth version updated on April 21, 2025.

## **Setting & Recruitment**

Participants will be recruited from the Specialist Outpatient Clinic at West China Hospital, Sichuan University. Individuals who meet the eligibility criteria will be informed about the trial procedures and enrolled upon providing written informed consent; those who do not meet the criteria will receive standard treatment in accordance with the trial protocol. To ensure an

adequate sample size, standardized training and supervision will be provided to researchers, improving the success rate of informed consent acquisition. The trial aims to recruit 78 participants, and additional strategies (e.g., referrals from medical examination centers or relevant departments, poster campaigns) will be employed to facilitate timely enrollment. Recruitment will commence within one year of the scheduled enrollment date and will proceed based on site readiness. Details on data collection and intervention administration are available in Supplemental Material II. All eligible participants who agree to partake in the trial will be randomly assigned and briefed on the required procedures and written informed consent (accessible in Supplemental Material III) must be provided prior to enrollment. Baseline data for both groups will be gathered via a questionnaire administered before the intervention in Room 902 of the Special Needs Outpatient Department, collecting demographic information (e.g., gender, age, height, weight, occupation, education), potential causes of back pain, physical activity level, medical and exercise treatment history, duration of low back pain, severity of low back pain (current, worst, and least), level of functional impairment, and types of pain avoidance behaviors (see Supplemental Material II). Experienced physical therapists, who are independent of the trial design, intervention, and statistical analysis, will perform outcome measurements at baseline, after the 4-week intervention, and after the 8-week intervention, as illustrated in Figure 1.

### ***Eligibility criteria and Consent***

If a patient expresses interest in participating, researchers will evaluate their eligibility based on the study's inclusion and exclusion criteria (Table 1). Both physicians and researchers will provide prospective participants with consent material detailing the context of the trial, the relevant population, interventions, risks and advantages of participating, along with rights and obligations. Individuals who agree to participate will be given thorough written information about the goals and methods of the study, and they will be asked to sign three informed consent forms. One copy will be kept by the participants, one will be electronically scanned on the first visit by the physician, and the third copy will be safely preserved by the Sichuan University Ethics Committee.

